### **6.3 Measurements**

#### **i) Anthropometry and blood pressure**

Clinical measurements will include weight, height, BMI, waist circumference and blood pressure, taken by trained personnel using appropriate calibrated measuring tools. The participants will be instructed to wear light clothing and without shoes during measurements. Height and weight will be taken using a stadiometer and SECA digital scale, to the nearest 0.1 cm and 0.1 kg respectively and these measurements will be used to calculate Body Mass Index (BMI). BMI is calculated using the formula of weight in kg divided by height in m^2 (kg/m^2). In this study, the BMI is according to the revised cut-offs for Asian classification [57]. Patients with BMI between 23.0 kg/m^2 to <27.5 kg/m^2 is classified as overweight and a BMI of  $\geq 27.5$  kg/m^2 is classified as obese. Waist circumference will be taken to nearest 0.1 cm using SECA measuring tape and according to the WHO procedure (1995) [58]. Blood pressure will be measured with an automatic digital blood pressure monitor (OMRON HEM -907 model). The participants are required to be seated while two measurements are taken for average value after resting for at least 10 to 15 minutes.

#### **ii) Biochemical**

All participants will be required to fast overnight prior to each blood test for a minimum of eight hours. Plasma levels of fasting glucose and 2 hour post 75 g glucose load are assayed using the GLUC method for the Dimension Clinical Chemistry System (by Siemens, Newark, U.S.A). To minimize the influence of any acute incidental reaction, participants will be advised not to engage with strenuous physical activity for at least 12 hours before blood sampling. The Bio-Rad D-10 Hemoglobin A1C program system will be used for the percentage determination of HbA1C in human whole blood using ion-exchange high performance liquid chromatography method (HPLC).

The total cholesterol (TC), high density lipoprotein (HDL) and triglyceride (TG) are analyzed using the CHOL, AHDL and TGL method for the Dimension Clinical Chemistry System (by Siemens, Newark, U.S.A). Whereas, low density lipoprotein (LDL) is calculated using the Friedewald equation [59].

### **iii) Physical activity**

Physical activity (PA) will be measured using the short form International Physical Activity Questionnaire (IPAQ). The IPAQ was translated and validated in different languages including the Malay version of IPAQ [60]. Participants' weekly MET-minutes of walking, moderate and high intensity activity will be summed up and categorized into low physical activity (i.e., if < 600 MET-minutes/ week), moderate physical activity (i.e., if 600 -1500 MET-minutes/ week) and high physical activity (i.e., if  $\geq$  1500 MET-minutes/ week) [61]. The dietary intake will be measured using the 24 hours diet recall. Participants' are asked to record their dietary intake for three days (two week-days and one week-end) and the average measurement will be taken.

### **iv) Health-related quality of life**

The health-related quality of life (HRQOL) will be assessed using a bilingual version of short-form health survey (SF-36) questionnaire. The SF-36 was translated and validated in Malaysia [62] and the Malay version of SF-36 has shown to be reliable and valid with Cronbach alpha coefficient for all subscales exceeded the recommended 0.70 [63]. It contains 36 items which measures eight health domains; physical functioning (PF), role-physical (RF), bodily pain (BP), general health (GH), vitality (VT), social functioning (SF), role-emotion (RE) and mental health (MH)[64]. The eight domains will be scored from 0 to 100 indicating worst to best possible health.

All the scores will further summarized into the Physical Component Summary score (PCS) and Mental Component Summary score (MCS).

#### **6.4 Outcome measures**

The primary outcome measures for this study are fasting blood glucose, 2-hour plasma glucose and HbA1C. Secondary outcome measures are weight, BMI, waist circumference, Total cholesterol, Triglyceride, LDL cholesterol, HDL cholesterol, Systolic and Diastolic blood pressure, physical activity, diet intake and HRQOL. All these will be taken at baseline, six months and twelve months except for HRQOL that will be measured at baseline and twelve months. The primary assessment time-point of this study is at 6-month to measure the immediate effect of the intervention. The final visit which occurred at 12-month will be used to measure sustainability of the intervention.

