### **ABSTRACT**

**Background:** Although recent evidence shown that lifestyle interventions are effective and can be delivered in an affordable manner in the community, more studies need to be done. This is due to the fact that more than 70% of people with diabetes live in low and middle income countries, and the largest increases in diabetes prevalence is predicted to occur in the Asian region. However, studies from developing countries are scarcely documented. Therefore, the objective of this study is to contribute to the growing body of literature on the effects of community-based lifestyle intervention among adults at high risk of type 2 diabetes.

**Methods:** This is a quasi-experimental study comparing a community-based healthy lifestyle intervention program (Co-HELP) to the usual care (UC) in high risk adults from two semi-urban communities. The population of this study is the high risk adults for type 2 Diabetes that will be recruited through the health screening in the community. The strategy of intervention is by using group-based approach, collaborative efforts with professionals in the initial stage but later on will be handled completely by community health workers and the peer educators. This is an innovative expansion of diabetes prevention program in the community setting that will determine the feasibility of Malaysia Diabetes Association as the empowered community partners.

**Outcome measures:** The primary outcome measures are change in the fasting blood glucose, 2-hour plasma glucose and HbA1C. Secondary outcome measures include weight, BMI, waist circumference, total cholesterol, triglyceride, LDL cholesterol, HDL cholesterol, systolic and

diastolic blood pressure, physical activity, diet and health-related quality of life (HRQOL). The outcomes will be analyzed at regular intervals within a period of one year.

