##### **b) Specific objectives:**

- i) Primary objective-to determine the changes in blood glucose (FPG, 2hPG and HbA1C) among adults who received community-based lifestyle modification intervention as compared to the usual care intervention.
- ii) Secondary objective-to determine the changes in other cardiometabolic risk factors (ie; total cholesterol, HDL cholesterol, Triglycerides, Blood Pressure, weight, BMI, waist circumference), dietary intake, physical activity and health-related quality of life (HRQOL) among adults who received community-based lifestyle modification intervention as compared to the usual care intervention..

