## **5.8 Sample size estimation**

Referring to the study by Kulzer et al [42] using a group based lifestyle intervention study to prevent diabetes mellitus; mean weight loss and duration of physical activity per week were significantly higher while fasting glucose was significantly lower in the intervention group compared to the control group after 12 months follow up. Using the sample size calculation from STATA

program, with power of 80% and significant level preset at 0.05, using different indicators, the calculated sample sizes are as the following:

|                                        | Duration of physical activity (minutes) | Fasting blood glucose (mg/l) | Weight loss (kg) |
|----------------------------------------|-----------------------------------------|------------------------------|------------------|
| Mean difference 1                      | 17.9                                    | 1.8                          | 3.8              |
| Mean difference 2                      | 46.6                                    | -4.3                         | 1.4              |
| Standard deviation 1                   | 63.8                                    | 13.1                         | 5.2              |
| Standard deviation 2                   | 95.5                                    | 11.3                         | 4.1              |
| Calculated Sample size group 1         | 122                                     | 64                           | 60               |
| Calculated Sample size group 2         | 122                                     | 64                           | 60               |
| Final sample size (with 30% attrition) | 122 x 2 = 244                           | 83 x 2 = 166                 | 78 x 2 =156      |

Based on the above, the largest sample size will be used in this proposed study to ensure adequate power for most outcome measures. Therefore, 244 subjects will be require for this study.

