## 12.0 DATA ANALYSIS

Patient demographic, clinical variables and baseline value will be compare between groups by the use of independent t-test for normally distributed variables and Mann Whitney test for non-normally distributed variables. Chi-square test will be use for discrete variables. The analysis will be done according to the intention-to-treat (ITT) principle. The missing values will be replaced by

the last readings carried forward. General Linear Model repeated measures ANOVA will be conducted to examine the changes overtime within-groups and between-groups. In the repeated measures model, the baseline value of co-morbidities, medication used, smoking and alcohol consumption were used as covariates in analysis for lipid profiles and blood pressure measurements. The outcome results from baseline to follow up at 6 months and 12 months will be presented as mean group differences, 95% confidence interval, p value and partial eta squared. A p-value of  $<0.05$  was considered statistical significant and effect size as proposed by Cohen (1998) were (0.01= small effect, 0.06= moderate effect and 0.14= large effect [65]. All statistical analysis will be performed using the SPSS software version 19.0 (SPSS Inc, 2009, Chicago, Illinois)

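### Three equal primary outcomes share one unadjusted 0.05 threshold with no success rule; if any one success counts, the false-positive risk is about 8–14%, not 5%

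*Protocol*

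**What the plan says.** The protocol names the same three primary outcomes in three places and ranks them in none.

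- Abstract: "The primary outcome measures are change in the fasting blood glucose, 2-hour plasma glucose and HbA1C".
- Section 4.0 b): "Primary objective-to determine the changes in blood glucose (FPG, 2hPG and HbA1C) among adults who received community-based lifestyle modification intervention", compared with usual care.
- Section 6.4: "The primary outcome measures for this study are fasting blood glucose, 2-hour plasma glucose and HbA1C".

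Section 6.4 also settles the timing: "The primary assessment time-point of this study is at 6-month to measure the immediate effect of the intervention". The 12-month visit is assigned to sustainability.

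Section 12.0 applies a single criterion to all outcomes. A p-value below 0.05 "was considered statistical significant and effect size as proposed by Cohen"; the rest of that sentence gives effect-size cut-offs. The section reports group differences, confidence intervals and p-values for both 6 and 12 months. It gives no order of testing, no division of the significance level, and no statement that one or all of the primary outcomes must succeed.

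Section 5.8 sizes the trial "with power of 80% and significant level preset at 0.05, using different indicators". The indicators are physical activity, fasting glucose and weight, so only one of the three primary outcomes is sized, and at the full 0.05.

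**The concern.** The general objective in section 4.0 a) is a single overall question: does the programme work better than usual care? The protocol gives three equal routes to an answer, each at 0.05, and does not say how the three results combine. A report could find one of the three significant, call the programme effective, and be consistent with the protocol as written. The 5% level would then describe each test but not the conclusion.

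The opposite rule, all three required, would be sound on error rate. It would, however, depend on power for 2-hour glucose and HbA1C, for which section 5.8 gives no inputs. Under either reading the criterion for primary success is open, and it should be closed before outcome data are seen.

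**Working it through.** **Inputs from the protocol.** Three primary outcomes at 6 months (section 6.4). Threshold 0.05 for each (section 12.0). Fasting glucose in section 5.8: mean changes 1.8 and −4.3, SDs 13.1 and 11.3, power 80%, 64 per group. Planned total 244, that is 122 per group. Attrition 30%.

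**Step 1: reproduce the protocol's figure.** The protocol does not state whether the test is two-sided. Taking it as two-sided:

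n per group = (z for 0.975 + z for 0.80)² × (SD1² + SD2²) / difference²
= (1.960 + 0.842)² × (13.1² + 11.3²) / 6.1²
= 7.85 × 299.30 / 37.21 = 63.1, rounded up to 64.

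This matches the stated 64. A one-sided test would give 50, so the planned level is an unadjusted two-sided 0.05.

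**Step 2: chance of at least one false positive among three true-null outcomes.** If independent: 1 − 0.95³ = 0.143.

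For a common pairwise correlation r, with c = 1.960, Φ and φ the standard normal distribution and density functions, and the integral taken over x:

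1 − ∫ [Φ((c − √r·x)/√(1−r)) − Φ((−c − √r·x)/√(1−r))]³ φ(x) dx

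| Assumed r | At least one p<0.05, either direction | At least one favouring the intervention |
|---|---|---|
| 0 | 14.3% | 7.3% |
| 0.3 | 13.6% | 6.8% |
| 0.5 | 12.5% | 6.3% |
| 0.7 | 10.9% | 5.5% |
| 0.8 | 9.8% | 4.9% |
| 0.9 | 8.4% | 4.2% |
| Nominal | 5% | 2.5% |

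The protocol gives no correlations, so the whole range is shown. The table applies only if success on any one outcome counts.

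**Step 3: cost of control, for fasting glucose.** Holm's strictest step is 0.05/3 = 0.0167, with z = 2.394.

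Sample size for 80% power: (2.394 + 0.842)² × 299.30 / 37.21 = 84.2, rounded up to 85 per group.

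Completers if the protocol's 30% attrition is applied to its planned 122 per group: 122 × 0.70 = 85.4, about 85.

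Power with 85 per group: the standard error is √(299.30/85) = 1.876, and 6.1/1.876 = 3.251.
- At 0.05: Φ(3.251 − 1.960) = Φ(1.291) = 90%.
- At 0.0167: Φ(3.251 − 2.394) = Φ(0.857) = 80%.

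With all 122 per group completing, power is 97% at 0.05 and 93% at 0.0167.

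**Step 4: what cannot be computed.** Section 5.8 gives no effect or SD for 2-hour glucose or HbA1C, so neither Holm power nor all-three power can be worked out for the family. The fasting glucose inputs come from a source study with 12 months of follow-up, whereas the primary comparison here is at 6 months.

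**The case against.** **This could be left to the analysis plan.** An alpha split or testing order often is, and a separate plan may exist. That limits the point to what the protocol itself fixes: three equal primaries, one threshold for all, and a sample size at that threshold. Section 5.7 refers the analysis to a later section of the same document, and section 12.0 goes as far as naming tests, missing-data handling, covariates and the significance level. The stated rule, followed as it stands, does not protect an overall effectiveness claim. The point survives, at moderate strength.

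**The protocol never says that any one success suffices.** This is correct, and the 8–14% is conditional on that reading. Requiring all three would remove the inflation. But that rule is not stated either, and it would need power that the protocol does not show.

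**The three outcomes are closely related.** Section 4.0 b) groups them as blood glucose, so high correlation is plausible. This stands, and is why the range extends down to 8.4%. Even there the figure exceeds 5%.

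**A reader might count six tests**, because section 12.0 reports p-values at both visits. The protocol does not support that count as the primary family: section 6.4 names 6 months as primary and gives 12 months a different purpose.

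**Multiplicity is not the largest threat.** Sections 5.2 and 5.6 allocate by community, one per arm. Individual-level p-values therefore carry any difference between the communities, and no adjustment across outcomes removes it. This stands as a limit on what the fix achieves.

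**Conclusion.** The point holds in conditional form. The protocol fixes three primary outcomes of equal rank and one unadjusted 0.05 threshold, and leaves primary success undefined. If any one significant 6-month result counts as effectiveness, the two-sided false-positive risk is about 8–14%, for assumed pairwise correlations from 0.9 down to 0. Counting only errors in favour of the intervention, it is about 4–7% against 2.5%.

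Two stronger conclusions might be inferred and are not supported. The trial's error rate is not shown to be 8–14% unconditionally, because the any-success rule is an inference from silence. Nor is correction shown to be affordable across the family: that is demonstrated for fasting glucose alone, with inputs from a 12-month source. The matter should be corrected, but it does not invalidate the data.

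**What to change.** Add one paragraph, in matching terms, to sections 6.4 and 12.0, choosing one of two options.

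1. Define the primary family as fasting glucose, 2-hour glucose and HbA1C at 6 months, tested by Holm's procedure at an overall two-sided 0.05 (smallest p-value against 0.0167, next against 0.025, last against 0.05, stopping at the first failure). Claim effectiveness only for outcomes that pass.
2. Name fasting glucose at 6 months as the single primary outcome at two-sided 0.05, and make 2-hour glucose and HbA1C secondary.

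Under either, state that 12-month results are supportive, in line with section 6.4.

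Option 1 lowers fasting glucose power from about 90% to about 80% at Holm's strictest step with about 85 completers per arm, which is still the protocol's 80% target. That is the worst case, since later steps are less strict. The cost for the other two outcomes is unknown until the protocol supplies an effect and SD for each. Option 2 costs no fasting glucose power. Neither changes recruitment or visits. The paragraph should not claim more than control across outcomes: the one-community-per-arm design needs its own treatment.

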#### **7.0 HOW TO ENSURE GOOD RESPONSE RATE?**

- i) Good response rate from the participants can be achieve by conducting regular meeting with the study partners to discuss about the progress and problems encounter. Immediate action will be taken if any problems arise.
- ii) Community volunteers will play their role in terms of social visits and follow up for participant failed to turn up.
- iii) To prescribe lifestyle modification interventions that are tailored with the Malaysian lifestyle and culture.
- iv) To try our best to arrange the intervention activities during weekend and flexible with the participant's time

## 8.0 STUDY VARIABLES

| Independent variables |                            | Dependent variables                                                         |
|-----------------------|----------------------------|-----------------------------------------------------------------------------|
| i.                    | Age                        | a) Changes in Weight (kg)                                                   |
| ii.                   | Gender                     | b) Changes in Body Mass Index (kg/m  )                          |
| iii.                  | Ethnic group               | c) Changes in waist circumference (cm)                                      |
| iv.                   | Education level            | a) Changes in fasting plasma glucose (mmol/L),
2hPG (mmol/L) and HbA1C % |
| v.                    | Socio-economic status      | b) Changes in TC, HDL, LDL, TG (mmol/L)                                     |
| vi.                   | Family history of Diabetes | c) Change in SBP and DBP (mmHg)                                             |
| vii.                  | History of smoking         |                                                                             |
| viii.                 | History of alcohol intake  |                                                                             |

## 9.0 STUDY MEASUREMENTS AND INSTRUMENTS

| Measurements        | Instruments                                                                                                            | Quality      |
|---------------------|------------------------------------------------------------------------------------------------------------------------|--------------|
| Physical activity   | Physical Activity Readiness Questionnaire (PAR-Q)
International Physical Activity Questionnaire (IPAQ – short form) | Validated    |
| Diet                | 24 hr diet recall                                                                                                      | Validated    |
| Weight              | Electronic weighing machine                                                                                            | Calibrated   |
| Height              | Stadiometer                                                                                                            | Standardized |
| Waist circumference | Measuring tape                                                                                                         | Standardized |
| Blood Glucose       | Laboratory analysis of serum plasma glucose                                                                            | Calibrated   |
| Lipid Profile       | Laboratory analysis of serum lipid                                                                                     | Calibrated   |
| Blood pressure      | Digital blood pressure                                                                                                 | Calibrated   |

## 10.0 DATA COLLECTION

The data collection for both groups will be done at the same interval:

- i) 1st data collection : At baseline
- ii) 2nd data collection: After 6 months
- iii) 3rd data collection: After 12 months

**Table 8: Summary of data collection and time interval**

| Measurements  | Screening | Baseline | 6-month | 12-month |
|----------------------|------------------|-----------------|----------------|-----------------|
| Questionnaire |                  |                 |                |                 |
| Socio-demography     | X                |                 |                |                 |
| PAR-Q                | X                |                 |                |                 |
| IPAQ-Short form      |                  | X               | X              | X               |
| 24-hour diet recall  |                  | X               | X              | X               |
| SF-36 HRQOL          |                  | X               |                | X               |
| Anthropometry |                  |                 |                |                 |
| Weight               | X                | X               | X              | X               |
| Height               | X                | X               | X              | X               |
| BMI                  | X                | X               | X              | X               |
| Waist circumference  | X                | X               | X              | X               |
| Clinical      |                  |                 |                |                 |
| Blood Pressure       | X                | X               | X              | X               |
| Biochem       |                  |                 |                |                 |
| RBS                  | X                |                 |                |                 |
| FPG                  |                  | X               | X              | X               |
| 2-hPG                |                  | X               | X              | X               |
| HbA1C                |                  | X               | X              | X               |
| Total cholesterol    |                  | X               | X              | X               |
| HDL cholesterol      |                  | X               | X              | X               |
| Triglycerides        |                  | X               | X              | X               |

